# 4. Project DESIGN

### 4.1. DESIGN

This project will utilise a mixed-methods approach. Study 1 is a prospective pre post study to evaluate the impact of the multimodal intervention on dementia awareness and risk. Study 2 is a qualitative study designed to assess the experience of participants’ who engaged in the Brain Bootcamp. Study 3 is a feasibility study to determine the acceptability, feasibility and discriminant validity of a new virtual reality technology to assess cognition in older adults.

### 4.2. EXPECTED PARTICIPANT NUMBERS

| Study 1 | Study 2 | Study 3 |
| --- | --- | --- |
| 500 older adults | 40 older adults | 100 older adults and 100 adults |

### 4.3. SETTINGS

| Study 1 | Study 2 | Study 3 |
| --- | --- | --- |
| Data will be collected from older adults living within New South Wales (NSW) | Data will be collected from older adults living in NSW who participated in Study 1 | Data will be collected from older adults and young adults living in NSW |

# 5. STUDY PARTICIPANTS

### 5.1. INCLUSION AND EXLUSION CRITERIA

**Study 1 and Study 2**

**Inclusion**

- Community-dwelling individuals aged 65 years or more on date of consent.
- Access to the internet in order to complete the online assessments.
- Living within NSW.
- Ability to communicate sufficiently in English.

**Exclusion**

- Diagnosis of dementia.
- Diagnosis of severe depression.
- Unable to provide informed written consent.

**Study 3**

**Inclusion**

- Community-dwelling adults aged 18 and over
- Access to the internet in order to complete virtual reality component
- Living in NSW
- Ability to communicate sufficiently in English

**Exclusion**

- Unable to provide informed consent
- Diagnosis of dementia
- Diagnosis of severe depression
- Poor vision
- Unable to follow verbal commands
- Diagnosis of aphasia
- Impairment of kinetic abilities (ability to use mouse)

# 6. STUDY PROCEDURES

6.1. Projected STUDY timeline

The study is predicted to span 24 months. A brief outline is provided in **Table 1**

**Table 1:**

|  | Year 1 | Year 2 |
| --- | --- | --- |
| General admin | --Preparation for ethics application and approval  --Reports: progress | Reports: final  Paper write up and publication |
| Study 1 | --Preparation of Brain Bootcamp box  --Delivery of Brain Bootcamp box  --Participant baseline assessment  --Participant follow-up assessment | --Participant follow-up assessment  --Data entry and cleaning  --Statistical analysis |
| Study 2 | --Data collection for process evaluation | --Data entry and cleaning  --Statistical analysis |
| Study 3 | --Virtual reality design and development  --Recruitment of participants  --Administration of traditional and novel assessments  --Feedback survey completion | --Administration of participant and novel assessments  --Feedback survey completion  --Data entry and cleaning  --Statistical analysis |

### 6.2. STUDY PLAN

**Overview**

**Study 1**

This project aims to explore the effectiveness of Brain Bootcamp in improving dementia awareness and knowledge of dementia risk factors amongst the community.

Participants will be adults aged 65 years and older and meet the inclusion criteria (See Section 5.1.)

We will recruit community-dwelling older adults from the general population of NSW through a widespread advertising strategy (**see 6.3**) to invite them to register for Brain Bootcamp and participate in our online Qualtrics surveys. They will be asked to complete our dementia awareness survey, motivation, and complete information on their basic demographics (e.g. age, gender, education, income) as well as information pertaining to brain health risk profile (**see Section 7**). Upon completion they will receive a Brain Bootcamp Box with four physical items and their personalised brain health risk profile based on the LIBRA index[19] to encourage them to adopt healthier habits and behaviours.

Three months after completing the baseline surveys, participants will be asked to complete a follow-up survey which will be the same as the baseline surveys to determine if there has been any change. Participants will receive their updated brain health risk profile.

**Study 2**

A sample from Study 1’s participants will be invited for semi-structured interviews at the end of the follow-up assessments. Interviews will explore their views of the information they received from their profile, whether they have accessed the resources in their Brain Bootcamp pack, any health behaviour change goals, how they did/did not incorporate recommendations into their daily life, and their perception of the overall impact of the initiative. We will also investigate why participants did not complete the trial by including a sample of those who dropped out.

An opt-in approach to recruitment of participants has been selected, to reduce any perceived pressure, and ensure that clients’ decision to participate is made freely. Participants will receive the following information prior to choosing to take part in the study:

- There will be no consequence or penalty associated with choosing not to participate, including any kind of consequence regarding the Brain Bootcamp box previously sent to them.
- Their responses will remain entirely anonymous, and no individual participant will be identified when reporting results from the interviews and focus groups, or any other data analyses.

**Study 3**

General public participants who meet the inclusion criteria and are over the age of 18 will be recruited to participate in both a virtual reality cognitive screener and a traditional telephone based cognitive screening test. For the older adults, a sub-set of older adult participants from Study 1 will be contacted via email to see if they are interested in participating. This will be based on their scores in the brain health risk profile, identified using the LIBRA index, which is shown to be a valid predictor of the development of dementia [19-21]. Younger adults will be recruited from the general public via social media and other relevant channels. All participants will be provided with an opportunity to participate in a feedback survey after they have completed the virtual reality screener. Questions will be about the acceptance, perception and experience of virtual reality.

### 6.3. PARTICIPANT RECRUITMENT AND SCREENING

**Study 1 and Study 2**

Participants will be consecutively recruited through a widespread advertising strategy, including standardised public advertisements and flyers disseminated at general medical practices, community newsletters, local print media, flyers and radio in NSW (**Figure 1**). The general population who are interested in receiving a Brain Bootcamp Box will register online (<http://www.brainbootcamp.com.au>) between January and March 2021. Upon registration they will be asked questions pertaining to the eligibility criteria and eligible members will be prompted to proceed and participate in the campaign. Eligible participants will be asked to provide informed consent on the online registration form. Research assistants will keep a screening log of potentially eligible participants and reasons for exclusion or possible refusal will be recorded.

**Figure 1. Advertising strategy**

[figure not shown]

**Study 3**

General public participants older adult and younger adult participants will be recruited via (i) study 1 or (ii) advertisements circulated via social media and researcher contacts. Researchers will determine their eligibility by checking them against the eligibility criteria.

### 6.4. PARTICIPANT ENROLMENT

**Study 1**

The participant will be enrolled into the study after the informed consent process has been completed. We request general public participants to include identifiable information on the surveys if they wish to complete the surveys at two time points. Upon completion of the first survey, participants will receive a study enrolment number which will be documented on all study documents and pre-populated on their second survey to enable the research team to link their results.

**Study 2**

Participants from study 1 will be contacted by researchers to participate in study 2 in which they will provide online consent and be enrolled into the study once this has been provided. Potential participants for the interviews will be assessed against the inclusion and exclusion criteria. If they meet all criteria they will then be enrolled in the study once informed consent is received

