**Study 2**

Study 2 participants are consenting to (1) participate in a telephone interview to provide feedback on the campaign. At time of follow-up assessment, participants will be contacted and provided with an opportunity to provide their opinion on the Brain Bootcamp campaign. They will be asked to provide consent to participate in a telephone interview that will be recorded and transcribed. We will attempt to reach out to individuals who dropped out of the study (i.e. those who did not update their brain health profile at three-month follow-up).

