**Study 3**

Study 3 will include community-dwelling participants aged 18 years and over. Study 3 participants are consenting to participate in a (1) using identifiable information provided in study 1 to be contacted for study 2; (2) participate in a virtual reality cognitive screener or; (3) participate in a traditional cognitive assessment via telephone (4) participate in a feedback survey about the acceptability and feasibility of the Virtual Reality Cognitive Screener .

Participants from Study 1 will be given the opportunity to participate in Study 3 based on their brain health profile at baseline. Adults from the general public participants not involved in the Brain Boot Camp campaign will also be recruited to participate in the study. For the virtual reality cognitive screener, participants will provide online consent and receive a link to participate in the virtual reality screener online. For the traditional cognitive assessment via telephone, researchers will also seek verbal consent at time of administration before undertaking the assessment to ensure participants understand the study. After completion of the virtual reality screener participants will be invited to participate in a brief online feedback survey.

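### Study 2 sets out to interview people who did not return the online follow-up survey, but enrols them only if they have internet access and consent online

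*Protocol*

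**What the plan says.** The aim is in Protocol section 6.2, Study 2: "We will also investigate why participants did not complete the trial by including a sample of those who dropped out". Section 6.5 defines a drop-out as someone whose brain health profile was not updated at three months, which in practice means someone who did not return the online follow-up survey. Section 8.1 makes drop-outs a target of the theoretical sampling and estimates 40 interviews in all.

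The enrolment rule is in section 6.4, Study 2. Study 1 participants are contacted for the interview, "in which they will provide online consent and be enrolled into the study once this has been provided". The section continues "Potential participants for the interviews will be assessed against the inclusion and exclusion criteria" and then "If they meet all criteria they will then be enrolled in the study once informed consent is received". No exception is made for drop-outs.

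Section 5.1 has one list for Studies 1 and 2. It includes "Access to the internet in order to complete the online assessments" and "Living within NSW". It also requires community dwelling, a minimum age and sufficient English. It excludes people with a diagnosis of dementia or severe depression and people who cannot give informed consent in writing.

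The interview itself is by telephone. Section 6.5 says "They will be asked to provide consent to participate in a telephone interview that will be recorded and transcribed" and does not state there how that consent is given.

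**The concern.** People are sought for these interviews because they did not complete an online task. The enrolment rule then asks for internet access and a further online task before they can take a telephone call. The stated purpose of the internet criterion is the Study 1 assessments, so it has no function for the interview.

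What is at stake is how well Study 2 can answer its own question about non-completion. The protocol describes no other way to learn why people stopped. The screening log in section 6.3 covers exclusions and refusals at entry, and section 6.8 lets participants withdraw without providing for a reason to be recorded. If those who stopped because of internet access or the online format cannot be reached, those reasons are the least likely to appear among the themes, although they bear directly on whether an online campaign suits this age group.

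**Working it through.** No statistical formula is involved. The check sets the provisions side by side and asks who is barred under each possible reading.

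1. **Who is sought.** Participants without a three-month profile update (6.5), to learn why they did not complete (6.2), chosen by theoretical sampling (8.1).
2. **How they are interviewed.** By recorded telephone call (6.5, 6.6).
3. **What enrolment requires.** All the shared criteria in 5.1, plus online consent (6.4).
4. **As of when the criteria are judged.** Section 6.4 does not say, so both readings need to be followed through.
   - *Status at the time of interview.* Every Study 2 candidate comes from Study 1 and was checked for eligibility at registration (6.3, 6.5). A second check adds something only if it looks at current status, so this is the natural reading. Under it, a drop-out is newly barred by loss of internet access, a move out of NSW, a move out of community dwelling, a new diagnosis of dementia or severe depression, or loss of capacity to consent.
   - *Status at Study 1 entry.* Nobody is newly barred by the criteria, and the sentence in 6.4 is redundant.
5. **What does not depend on the reading.** Online consent is a separate requirement in 6.4. Under either reading, someone who did not return an online survey must complete an online consent step before being interviewed.
6. **Consent wording elsewhere.** The shared list in 5.1 excludes people unable to consent in writing, whereas the Study 3 list in the same section does not specify writing. For the Study 3 telephone test, section 6.5 says "researchers will also seek verbal consent at time of administration before undertaking the assessment". Taking consent by telephone is therefore already part of this project.

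For scale only, section 8.1 assumes 25% drop-out. That gives 0.25 × 500 = 125 drop-outs in the planned cohort, or 0.25 × 403 = 100.75, about 101, on the section 8.1 sample size. These figures are the pool from which drop-outs would be sampled, not the number barred. The protocol gives no reasons for drop-out and no split of the 40 interviews between completers and drop-outs, so the number barred cannot be derived.

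**The case against.** The strongest reply is that section 6.4 never says the criteria are applied afresh. The internet criterion is worded around the online assessments, and every drop-out met it when completing baseline. Baseline consent in 6.5 already covers being contacted for a telephone interview, and the Study 2 text in 6.5 does not restrict consent to an online form. On this view only the timing is unspecified. That is fair as to the criteria, but it does not remove the online-consent requirement in 6.4.

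A reader might infer more than the protocol supports, in four ways:

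- **That health or relocation reasons in general are screened out.** They are not. Other illness, surgery, caring duties or fatigue exclude no one. Only the two diagnoses, inability to consent, leaving community dwelling or leaving NSW would. NSW is also the declared Study 2 setting in section 4.3, and excluding people who cannot consent is an ordinary safeguard.
- **That a particular share of drop-outs is lost.** No figure in the protocol supports one.
- **That the interviews would make Study 1's missing data look more benign than they are.** Study 2 samples theoretically until saturation and codes for themes (8.1, 8.2). It estimates no proportions of reasons, and no section uses it to assess missing data. Recruitment is also opt-in (6.2), so self-selection would shape the sample in any case.
- **That Study 3 already replaces other consent with verbal consent.** Verbal consent is sought there in addition, to make sure participants understand. It is a precedent for taking consent on the telephone, not clearly for substitution.

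**Conclusion.** The point holds in limited form. As written, section 6.4 puts an internet criterion and an online consent step in front of a telephone interview meant partly for people who did not return an online survey. Drop-outs who lost internet access (if current status is what is judged) or who will not complete another online form (on either reading) cannot be interviewed. This narrows the reasons for drop-out that Study 2 can reveal.

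The size cannot be calculated from the protocol. The effect is confined to the qualitative sub-study; no Study 1 outcome, sample size or analysis is touched. The conclusion about the internet criterion rests on the natural but unstated reading that eligibility is checked at the time of interview. The conclusion about online consent needs no such assumption. The change is worth making because it is cheap and serves a stated aim, but it is a modest correction.

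**What to change.** - In sections 5.1 and 6.4, state that the internet-access criterion does not apply to the Study 2 interview, and that the other criteria are those met at Study 1 entry, subject to current capacity to consent.
- In sections 6.4 and 6.5, allow consent to be given verbally and recorded at the start of the telephone interview, which is to be recorded anyway. Reconcile this with the requirement in 5.1 for consent in writing.
- Leave to the sponsor and the ethics committee whether the NSW setting in 4.3 and the diagnosis exclusions should bind participants who have moved or been newly diagnosed since entry. Those are questions of scope and ethics, not errors. If the limits are kept, report the drop-outs excluded on those grounds as a limitation.

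The cost is a few sentences, an ethics amendment for recorded verbal consent, and a check of capacity by the interviewer at the call.

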**Study 3**

The participant will be enrolled into the study after the informed consent process has been completed. We request general public participants to include identifiable information to ensure they can be contacted to participate in both the traditional cognitive assessment and virtual reality cognitive screener within the same week. Upon completion of the first screening assessment general public participants will receive a study enrolment number which will be pre-populated on the second screening assessment to enable the research team to link their results. Study 1 participants who wish to participate in study 3 will continue to use their study 1 enrolment number. After completing the virtual reality screener participants will be invited to participate in a short online feedback survey.

### 6.5. INFORMATION AND CONSENT

***Overview***

**Study 1**

Study 1 participants are consenting to (1) participate in an online surveys; (2) provide identifiable information at the first administration of surveys; (3) complete the same surveys 3 months later

Participants will visit our website (<http://makemywebdesign.com/brainbootcamp/>) and be able to register their interest in receiving the Brain Bootcamp box. Participants will be sent an automated email with a link to participate in the online survey. At this point, participants will indicate that they fulfill the inclusion criteria (i.e. no diagnosis of dementia, are aged 65 and over, are living within NSW, no diagnosis of severe depression). Participants who meet the eligibility criteria and wish to complete the survey will provide online consent before undertaking the assessments by ticking the consent box.

**Study 2**

Study 2 participants are consenting to (1) participate in a telephone interview to provide feedback on the campaign. At time of follow-up assessment, participants will be contacted and provided with an opportunity to provide their opinion on the Brain Bootcamp campaign. They will be asked to provide consent to participate in a telephone interview that will be recorded and transcribed. We will attempt to reach out to individuals who dropped out of the study (i.e. those who did not update their brain health profile at three-month follow-up).

**Study 3**

Study 3 will include community-dwelling participants aged 18 years and over. Study 3 participants are consenting to participate in a (1) using identifiable information provided in study 1 to be contacted for study 2; (2) participate in a virtual reality cognitive screener or; (3) participate in a traditional cognitive assessment via telephone (4) participate in a feedback survey about the acceptability and feasibility of the Virtual Reality Cognitive Screener .

Participants from Study 1 will be given the opportunity to participate in Study 3 based on their brain health profile at baseline. Adults from the general public participants not involved in the Brain Boot Camp campaign will also be recruited to participate in the study. For the virtual reality cognitive screener, participants will provide online consent and receive a link to participate in the virtual reality screener online. For the traditional cognitive assessment via telephone, researchers will also seek verbal consent at time of administration before undertaking the assessment to ensure participants understand the study. After completion of the virtual reality screener participants will be invited to participate in a brief online feedback survey.

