**Study procedure**

Studies 1, 2, 3 Participants will be recruited via a widespread advertising strategy using flyer dissemination, banners and existing networks.

Study 1 Online MQ Qualtrics surveys will be given to eligible participants to capture demographics, participant’s dementia awareness, mental health and mood, physical activity, cognitive activity, diet, motivation, social networks and quality of life information data (i.e., baseline).

Upon completion of surveys, participants will receive a Brain Bootcamp Box via post containing four physical items representing modifiable risk factors for dementia, an information booklet and their personalised brain health risk profile.

Three months after the Brain Bootcamp box has been sent out, participants will fill out the same assessments (i.e. follow-up)

Study 2 A sample of participants from Study 1 will be invited to participate in a semi-structured interview at follow-up to explore their views of the Brain Bootcamp Box, whether they did/did not implement behaviour change (goal-setting, frequency of item use) and their opinion on the impact of the initiative.

Study 3 Participants from the general public will be recruited as well as a sample of participants from Study 1 will be invited to participate in a traditional and novel memory assessment based on their baseline assessments and dementia risk profile. These participants will engage in a virtual reality cognitive screener developed by Macquarie University, a telephone assessment of their cognition and a feedback questionnaire for their experience with the virtual reality cognitive screener.

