**Study 3**

Participants will be recruited from the general public who are over 18. Study 1 participants will be contacted to give them an opportunity to participate in Study 3, based on their brain health risk scores. Information about their memory performance will be collected as outlined in **Section 7.** Both the Virtual Reality Cognitive Screener and telephone based cognitive assessment will take approximately 30 minutes to complete. A random selection of half of each of the younger and older adults participants will receive the traditional telephone cognitive assessment (Group A), whilst the other half will complete the Virtual Reality Cognitive Screener (Group B). Then, the groups will swap and Group A will complete the Virtual Reality Cognitive Screener , whilst Group B completes the telephone cognitive assessment. Both assessments will then be complete within a week of each other. After completion of the virtual reality cognitive screener, participants will be invited to provide feedback via a voluntary online survey about the feasibility and acceptability of their virtual reality experience.

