**Memory Performance:**

Traditional: Classification of cognitive status will be conducted by administering a 23 question Telephone Interview for Cognitive Status-Modified (TICS-M) either in person on over the phone. This will include scoring on name, date, age, phone number, ability to count backwards from 20 to 1, immediate recall of 10 words, counting backwards from 100 by 7, the naming of objects and concepts, repetition of phrases, the name of current political figures, tapping 5 times, naming opposites of common words, and delayed recall of 10 words. The maximum score is 50 points. The TICS-M will classify individuals as having no or minimal cognitive impairment (>40) or possible mild cognitive impairment (≤ 20) or moderate cognitive impairment (≤12). The TICS-M has been previously validated [43] with strong psychometric properties[44]. Prior studies have shown that the TICS-M has a high sensitivity in the detection of dementia[45, 46] but a low positive predictive value [43].

A further 5 minutes will be used to calculate the scores and to disseminate this finding to the participant at the end of the session. Whilst researchers are happy to discuss the findings further if the client wishes, if any participant has been identified as having a low memory score <27 they will be referred to their local GP to obtain a more comprehensive assessment.

Virtual Reality Cognitive Screener (VRCS): Developed using the Unity game engine, the application places the user on a virtual in a virtual restaurant modelled to be similar to an Australian café. The user’s role will be that of the waiter, needing to serve restaurant customers. The VRCS will be developed using Unity’s WebGL build option. This will allow the VRCS to run in current versions of most major web-browsers. Suggested browsers are (in no particular order) Microsoft Edge, Mozilla Firefox and Google Chrome. (Videos of the VRCS in development are uploaded in “Other Project Material”)

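### The protocol lets Study 1 participants have Study 3 cognitive testing, score feedback and possible GP referral before their three-month survey, and the uncontrolled pre-post comparison cannot separate that exposure from the box

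*Protocol*

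**What the plan says.** **Who is invited.** Section 6.5 (Study 3) states: "Participants from Study 1 will be given the opportunity to participate in Study 3 based on their brain health profile at baseline". The Summary (Study procedure) agrees: a sample from Study 1 is "invited to participate in a traditional and novel memory assessment based on their baseline assessments and dementia risk profile". Section 6.2 says "a sub-set of older adult participants from Study 1 will be contacted via email to see if they are interested in participating". It and section 6.6 base the choice on brain health risk scores without saying at which time point.

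**When they are tested.** The only timing rule is internal to Study 3. Section 6.6 states: "Both assessments will then be complete within a week of each other". Table 1 in section 6.1 lists "Administration of traditional and novel assessments" under Year 1, the same year as the Study 1 baseline survey, box delivery and follow-up. Study 3 assessments and Study 1 follow-up both continue into Year 2.

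**What they receive.** Section 7 (Memory Performance) sets aside five minutes after the TICS-M "to calculate the scores and to disseminate this finding to the participant at the end of the session", offers discussion of the result, and adds for low scorers: "low memory score <27 they will be referred to their local GP". The virtual reality score is withheld; participants see only how many orders they got right.

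**How Study 2 is handled.** Section 6.5 (Study 2) gives an anchor: "At time of follow-up assessment, participants will be contacted and provided with an opportunity to provide their opinion on the Brain Bootcamp campaign".

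**How Study 1 is analysed.** Section 4.1 describes a pre-post design and section 8.2 a paired t test on the brain health risk profile from baseline to three months. Nothing in the protocol flags or separately analyses people who also took part in Study 3.

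**The concern.** Being told a memory result, with a GP referral for some, is personal health information that the Brain Bootcamp box does not contain. It could plausibly act on dementia awareness, motivation and the LIBRA profile, all of which Table 2 lists as Study 1 outcomes. If it falls between the baseline and three-month surveys, it becomes a co-intervention in part of the sample.

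A randomised comparison could balance such an exposure across arms. A single-group pre-post comparison has nothing to set it against, so whatever the exposure does is added to the change credited to the box. The impact evaluation in section 7 asks how far an impact can be attributed to the initiative, and this overlap weakens the answer. Because invitation depends on the brain health profile, exposure is also linked to the baseline value of the outcome. A later comparison of tested and untested people would be confounded, including by regression to the mean.

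**Working it through.** **Step 1: is the overlap permitted?** Four statements, read together:
- Selection can use baseline data (Summary; 6.5), so a person can be invited as soon as the baseline survey is complete.
- The calendar in Table 1 overlaps in Year 1.
- The one-week rule (6.6) relates the two Study 3 assessments to each other, not to the Study 1 survey.
- Study 2 contact is placed at follow-up (6.2; 6.5); Study 3 contact has no such anchor.

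Testing before the three-month survey is therefore allowed. It is not stated to happen.

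**Step 2: how many could be exposed?** Inputs: 500 in Study 1 and 100 older adults in Study 3 (Summary; 4.2); 25% drop-out (8.1).
- Completers: 500 × 0.75 = 375.
- Ceiling if all 100 come from Study 1: 100/500 = 20% of those enrolled. If all 100 also complete: 100/375 = 26.7% of completers.
- If 50 come from Study 1: 50/500 = 10% and 50/375 = 13.3%.

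Sections 6.3 and 6.5 also allow older adults from the general public, so the number drawn from Study 1 is not fixed.

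Section 8.1 gives a required size of 403, which is not used here. It does not reproduce from its stated inputs: a two-sided paired t test with change 0.3, SD 0.5 and 90% power needs 32 completers, or 32/0.75 = 43 enrolled. That is a separate matter.

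**Step 3: what shift would follow?** Shift in mean change = share exposed × extra change c in those exposed. The documents give no value for c; 0.1 to 0.3 Z in the favourable direction is an assumption.

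| Exposed of 375 | c = 0.1 | c = 0.3 |
| --- | --- | --- |
| 50 (13.3%) | 0.013 | 0.040 |
| 100 (26.7%) | 0.027 | 0.080 |

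Against the planned change of 0.3 (8.1), the lower row is 0.027/0.3 = 9% to 0.080/0.3 = 27%, and the upper row is 4% to 13%.

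**Step 4: would it affect the test?** Taking the stated SD of 0.5 as that of the change, the standard error is 0.5/√375 = 0.026.
- If the full planned change is seen, removing the largest shift leaves 0.30 − 0.08 = 0.22. This is still 0.22/0.026 = about 8.5 standard errors, so significance is unaffected.
- If the box does nothing, the chance of a significant result favouring improvement is Φ(m/(s/√n) − 1.96), with m the shift, n = 375, s² = 0.25 + p(1 − p)c² and p the share exposed. With 100 exposed this is 18% at c = 0.1 and 85% at c = 0.3; with 50 exposed it is 7% and 33%. The nominal rate in that direction is 2.5%.

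**The case against.** The strongest reply is that the harm is only possible. Selecting on the baseline profile says who is invited, not when. Table 1 works in whole years, lists development of the virtual reality tool ahead of Study 3 recruitment in Year 1, and also provides for testing in Year 2. Registration for Study 1 was planned for January to March 2021 (6.3), so many follow-up surveys could be in before the screener is ready. All of this stands. A reader might infer that testing will precede follow-up, or that the Study 1 result will be contaminated; the documents say neither. They leave the order open.

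Other stronger readings also fail:
- **A particular risk stratum.** One might infer that the exposure sits in one risk group and so distorts the question of for whom the initiative worked. No section says which profiles are invited, and Study 3 needs both cognitively intact and impaired people.
- **Feedback and referral for everyone.** The result is fed back for the TICS-M only, and referral applies only to low scorers.
- **A known upward bias.** The direction is unknown. GP contact could bring to light conditions the survey asks about and worsen the profile. An extra 0.3 Z would equal the whole planned change, which is generous for a test of about 30 minutes plus a score.
- **Mood and health behaviour as outcomes.** Table 2 does not list them as outcomes in their own right.

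It can also be said that the lack of a control group is the larger weakness, that the protocol acknowledges it by planning for a randomised design (section 12), and that section 1 describes the screener under the Brain Bootcamp heading. The first two are true but do not justify adding an avoidable exposure. As to the third, the Summary lists what the box contains and testing is not in it.

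Finally, a sensitivity analysis might be left to an analysis plan. It can identify those exposed but cannot remove the exposure, and when people are invited and tested is conduct that the protocol itself must fix.

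**Conclusion.** The point holds as a gap in sequencing. The protocol permits testing, score feedback and possible referral inside the Study 1 outcome window, and the Study 1 design cannot separate their effect from that of the box.

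At the planned enrolment the exposure is capped at 20% of those enrolled, or about 27% of completers, and may be much lower. The illustrative shift of about 0.03 to 0.08 Z rests on three assumptions: all 100 older adults come from Study 1 and complete it, all are tested before follow-up, and each gains an extra 0.1 to 0.3 Z. A shift of that size would not overturn a result near the planned 0.3. It would matter for the estimate, and for significance if the box has little or no effect. The change is worth making because it is cheap and analysis cannot fully replace it.

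**What to change.** State in sections 6.2, 6.3 and 6.5 that Study 1 participants are contacted for, and tested in, Study 3 only after their three-month survey is submitted or, for non-responders, after the follow-up window closes. Selection may still use the baseline profile. The second condition is needed because requiring a submitted survey would shut Study 1 drop-outs, assumed to be 25%, out of this route and narrow the older Study 3 sample to adherent people. The window needs a defined close and one starting point: the Summary counts three months from dispatch of the box, section 6.2 from completion of the baseline surveys.

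If anyone was tested earlier, identify them through the enrolment number that Study 1 participants keep in Study 3 (6.4), and repeat the Study 1 analysis without them as a sensitivity analysis. Since selection depends on the profile, this is a check and not a repair.

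The cost is a short addition to the text and a delay of up to about three months in Study 3 testing of these participants, which Table 1 accommodates in Year 2. The feedback and referral arrangements need no change for this purpose.
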